**Transabdominal ultrasound scans—repeated measures**	
Date of ultrasound	Date (DD-MM-YYYY)
Uterus size	Length × width × depth (mm)
Cervix length	Number (mm)
Endometrium thickness	Number (mm)
Endometrial layers	1/2/3
Right/left ovary—size	Length × width × depth (mm)
Right/left ovary—number of small follicles	Not visualized/none/few/moderate/many
Right/left ovary—biggest follicle	Number (mm)
**Transfeminine youngsters variables**	**Value**
Puberty development a.m. Tanner	Tanner stage G1/G2/G3/G4/G5 Tanner stage PH1/PH2/PH3/PH4/PH5/PH6 Full puberty
Testis volume right/left	Volume (mL)
Opting for semen cryopreservation	Yes/no
**Semen cryopreservation—repeated measures**	
Date/age of semen collection	Date (DD-MM-YYYY)/age in years (number)
Azoospermia	Yes/no
Volume	Number (mL)
Concentration	Number (mill/mL)
Progressive motility spermatozoa	Percentage (%)
Non-progressive motility spermatozoa	Percentage (%)
Immotile spermatozoa	Percentage (%)
Did not complete semen collection	True/false
**Visits—repeated measures variables**	**Value**
Date of visit	Date (DD-MM-YYYY)
Blood pressure	Systolic blood pressure (number) Diastolic blood pressure (number)
**Other clinical data variables**	**Value**
Dual-energy X-ray absorptiometry (DXA) scan	Bone mineral density (BMD) (g/cm^2^) + Z-scores Total body fat percentage (%) Regional body fat percentage (%) Lean body mass (LBM) (g)
Growth chart	Height (cm) + standard deviation score (SDS) Weight (kg) + SDS Growth velocity (cm/year) + SDS Predicted adult height (cm) + SDS Target height (cm) + SDS
Bone age (a.m. Greulich-Pyle, BoneXpert)	Age in years (number)
Routine blood samples	Reproductive hormones Growth factors Thyroid hormones Vitamin D Lipids Liver-kidney function tests Hematocrit Hemoglobin
Biobank	Serum, plasma, DNA

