Puberty suppression in transmasculine individuals leads to some regression of breast tissue growth in the early pubertal stages and cessation of menses. In transfeminine individuals, further virilization is prevented, and testicular volume may decrease. Consequently, spermatogenesis and follicle maturation are arrested [16,17,18]. Puberty suppression with GnRHa is considered reversible, allowing the resumption of pubertal development, and is well tolerated in children with precocious puberty [16,18,19,20]. This pause in physical changes prevents the progression of incongruence between body appearance and gender identity, providing a period for further clarification before starting testosterone or estradiol treatment. However, potential adverse effects include headaches, mood changes, sterile abscesses from injections, hot flushes, and fatigue [16,18,20,21,22].

Masculinizing testosterone therapy leads to cessation of menses, increase in muscle mass and strength, fat redistribution, voice deepening, growth of facial and body hair, oily skin or acne, clitoral enlargement, and increased libido. It can lead to male pattern baldness and may affect fertility [16,22,23,24,25,26,27]. Additionally, breakthrough bleeding [28] and pelvic pain [29] have been reported during testosterone therapy. Feminizing estrogen and antiandrogen treatment leads to the development of breast tissue, fat redistribution, some decrease in facial and body hair, clearer and softer skin, reduction of libido, decrease in muscle mass and strength, reduction of testicular volume and sperm quality [16,22,23,26,27,30]. While puberty suppression is reversible when stopping treatment, most effects of GAHT are irreversible, such as breast development and body hair growth. 

Research related to gender incongruence in youngsters is still sparse, and current evidence is predominantly based on studies that are more than five years old. Emerging evidence, however, suggests potential health risks associated with hormone therapy. This includes the effects of GnRHa on bone health and brain development [31], the cardiovascular risks associated with GAHT, such as dyslipidemia and venous thromboembolism, and long-term risks, such as cancer and osteopenia [16,22,27]. Furthermore, there is a knowledge gap regarding the effects of hormone therapy on youngsters, including its impact on height, the development of secondary sex characteristics, and changes in body composition [32].

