### 1.2. Endocrine Treatment

Puberty suppression with GnRHa can be initiated from Tanner stage 2 [58,59,60]. GnRHa is given as depot injections. GAHT encompasses estradiol in transfeminine youngsters and testosterone in transmasculine youngsters. Sex steroid treatment doses are titrated over 6 to 12 months to reach adult serum levels of estradiol or testosterone. Testosterone therapy is initiated with daily transdermal gel applications. When adult doses are reached, intramuscular depot testosterone injections are offered as an alternative. Estradiol is administered with transdermal patches, gel, or tablets, depending on personal preferences. When testosterone concentrations in transmasculine youngsters reach adult levels, GnRHa is discontinued. GnRHa is continued parallel to estradiol therapy in transfeminine youngsters until referral to adult services.

Before hormone therapy, a somatic assessment is performed, i.e., a growth chart, including bone age and growth velocity; pubertal staging, if relevant; blood pressure; routine blood samples; and whole-body Dual-energy X-ray Absorptiometry (DXA) to evaluate body composition and bone mineral density. Routine blood samples consist of reproductive and adrenal hormones, sex steroids, growth factors, vitamin D, lipids, liver and kidney parameters, hematocrit, hemoglobin, and thyroid hormones, measured by liquid chromatography-tandem mass spectrometry (LC-MS/MS) or immunoassays. Semen cryopreservation is offered to transfeminine youngsters if biologically possible. Transabdominal ultrasound (TAUS) of the internal genitalia for transmasculine youngsters is performed on indications such as breakthrough bleedings but was performed routinely after one year of testosterone therapy until 2021. Routine visits every three to six months consist of blood samples (hormones and safety parameters), growth assessment if relevant, weight, blood pressure, and exploration of treatment results, effects, and side effects. DXA scans are performed every two years; bone age is repeated if indicated. Serum, plasma, and DNA are collected for a biobank at each clinical visit.

At 18 years of age, the youngsters are referred to continued care in adult gender services at one of three centers in Denmark [57].

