### 2.4. Analysis Plan

Data will be extracted from the REDCap database and analyzed in pseudo-anonymized datasets. Descriptive statistics will be used for sociodemographic characteristics, physical and mental health profiles, and treatment trajectories, i.e., mean (SD), median (IQ range), and frequencies (proportion). The data will be divided into subgroups according to whether hormone therapy is offered before the age of 18 years and whether they are referred to the Gender Identity Service before or after the onset of puberty. The subgroups will be compared according to sex assigned at birth, age of onset of gender incongruence, social transition, as well as sociodemographic background, mental health profiles, and global level of functioning. Physical health profiles of the youngsters in the hormone therapy subgroup will be compared to normative age- and relevant gender-matched reference populations. Group comparisons will be made using the Student’s *t*-test and Mann–Whitney/Wilcoxon tests as appropriate. Changes over time will be analyzed using time trend analysis for related data and paired *t*-tests or mixed model analysis. Regression models will investigate confounding factors related to treatment/no treatment outcomes and basic characteristics. If appropriate, analyses will be reported by year, i.e., trends in referral patterns and decision algorithms.

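### Bone density is recorded only as areal BMD with Z-scores and compared with norms matched on age and gender, so body size can bias the result in either direction

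*Protocol article*

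**What the plan says.** The bone density entry in Appendix A, Table A2 (other clinical data variables) is "Bone mineral density (BMD) (g/cm^2^) + Z-scores". The table does not say which reference the Z-scores use, and it lists neither bone mineral content nor bone area. The same block lists height with its SDS, growth velocity with its SDS, and bone age; Tanner stage appears elsewhere in the table.

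Section 2.4 states that the physical health profiles of treated youngsters "will be compared to normative age- and relevant gender-matched reference populations". For change over time it names time trend analysis, paired t-tests or mixed models. Neither statement mentions body size, pubertal stage or bone age.

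Section 1.2 says that puberty suppression may begin from Tanner stage 2. Youngsters have "whole-body Dual-energy X-ray Absorptiometry (DXA) to evaluate body composition and bone mineral density" before hormone therapy, and follow-up is described as "DXA scans are performed every two years; bone age is repeated if indicated".

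The Introduction lists emerging health risks of hormone therapy and opens that list with bone: "This includes the effects of GnRHa on bone health and brain development". It also names a knowledge gap on the effects of therapy, "including its impact on height, the development of secondary sex characteristics, and changes in body composition".

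**The concern.** Areal BMD is mineral mass divided by projected area. It does not account for bone depth, so of two bones with the same volumetric density the larger has the higher areal BMD. Matching on age and gender leaves any height difference between the cohort and its reference inside the Z-score.

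This matters here for two reasons. Some treated youngsters may still be growing when scanned, and scans are repeated, so a change in height SDS between scans can show up as a change in BMD Z-score. Also, the article does not say which gender is the relevant one for the reference. If it is experienced gender, birth-assigned females are set against male norms and birth-assigned males against female norms. At near-adult ages the first group would on average be shorter than its reference and the second taller, so the size bias would have opposite signs in the two groups.

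At stake is the reading of a safety result. The aims in section 1.3 include the safety of hormone therapy, and an unadjusted Z-score does not separate an effect on density from a difference in height.

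**Working it through.** The document gives no figure for bone outcomes, so there is nothing to reproduce. The check has three parts.

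**1. Is any size adjustment written?** The measure in Table A2 is areal, with an unstated Z-score basis. The comparison in section 2.4 is matched on age and gender. Neither place, nor any other in the article, mentions a height-adjusted or volumetric measure. The data for a height adjustment (height SDS) are on the extraction list.

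**2. How large could the effect be?** The inputs below are assumptions, not document figures.

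- Proportional scaling: if all bone dimensions change by a factor s at constant volumetric density, mass scales as s³ and projected area as s². Areal BMD then scales as s³/s² = s.
- Height CV: 3.5-4.5%. Areal BMD CV: 9-13%.
- Z shift = height SDS × CV(height) / CV(areal BMD).
- Share below Z = -2, with normal volumetric density and unit spread: Φ(-2 - shift).

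Per one height SDS, the smallest shift is 0.035/0.13 = 0.27 and the largest is 0.045/0.09 = 0.50.

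| Mean height SDS against reference | Shift in BMD Z | Share below Z = -2 |
|---|---|---|
| 0 | 0 | 2.3% |
| -0.5 | -0.13 to -0.25 | 3.1-4.0% |
| -1 | -0.27 to -0.50 | 4.2-6.7% |
| -2 | -0.54 to -1.00 | 7.2-15.9% |
| +1 | +0.27 to +0.50 | 0.6-1.2% |

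The same formula applies to change: a fall of 0.5 in height SDS between two scans would lower BMD Z by 0.13-0.25 with no change in volumetric density.

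**3. Which adjusted quantity answers the reference question?** Write Z = a + b × (height SDS) + e within the cohort. Least-squares residuals e average zero by construction, so their mean would show no deficit whatever the truth. The unadjusted cohort mean is a + b × (mean height SDS). The intercept a, which is the predicted mean BMD Z at height SDS 0, removes the size term and can be compared with the reference value of 0. External normative height-adjustment equations are the alternative.

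**The case against.** The strongest reply is that Table A2 is an extraction list. It does not say how bone health will be judged, and section 2.4 has one general sentence for all physical measures. A condensed article may leave derived variables to a fuller plan that is not shown, and height SDS, bone age and Tanner stage are all collected, so an adjustment stays possible. This stands as a limit on the claim: it cannot be said that an adjustment has been ruled out. It does not remove the point, because the article does name the comparison and its matching factors, and that comparison followed as written leaves body size in the bone result.

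Several stronger readings are tempting and are not supported:

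- **That treated youngsters will be read as having low density.** The bias runs both ways; in a group taller than its reference it would hide a deficit.
- **That growth is slowed in this cohort.** The Introduction treats the impact on height as a knowledge gap, and the share still growing at the scan is not given. Tanner stage 2 is only the earliest starting point, and Table A2 also has a full-puberty category.
- **That bone is the first safety concern named.** It heads the list of emerging risks, but the Introduction gives other adverse effects of GnRHa before it.
- **That the Z-scores are known to be age-based.** This is inferred from section 2.4; Table A2 does not give their basis.
- **That conclusions should rest on the adjusted score alone.** If treatment alters height, height at the scan is a post-treatment variable, and adjusting for it can remove part of a real effect on bone accrual. This objection stands in full and shapes the fix.

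**Conclusion.** The concern holds in a limited form. The article records bone density only as areal BMD with Z-scores of unstated basis, and names a comparison matched on age and gender. Read as written, this mixes bone size with bone density, with a sign that depends on the reference chosen.

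The plausible size is about 0.3-0.5 Z per height SDS. That rests wholly on the assumed CVs and on exact proportional scaling of bone with height. The actual height SDS of the treated group is not in the document, so the bias in this cohort cannot be computed and could be close to zero if the group matches its reference in height.

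The change is worth making because it is cheap and makes a stated safety outcome easier to interpret. It is not a flaw that undermines the study.

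**What to change.** 1. State which reference the BMD Z-scores use, including which sex, and use the same sex reference for height SDS.
2. Report a height-adjusted BMD Z-score beside the unadjusted one in both the reference comparison and the analysis of change, using height SDS at the scan date.
3. For the reference comparison, use external normative height-adjustment equations or the model-predicted mean BMD Z at height SDS 0. Do not use within-cohort residuals.
4. Interpret the two scores together. A deficit or fall seen only in the unadjusted score should not be attributed to loss of bone density. State that height may lie on the treatment pathway, so that the adjusted score supplements the unadjusted one and does not replace it.

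The cost is one more derived variable, one more column in the bone table, and the matching of heights to scan dates. Some scans will have no matching height and will drop out of the adjusted analysis; their number should be reported.
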